**Methods/design:**

A 6-month randomized intervention with 6-month follow-up is conducted from January 2013 to December 2015. The target sample size for intervention is 200 postmenopausal women and middle-aged men aged 50–65 year-old with pre-diabetes and NAFLD. The qualified subjects are randomized into 4 groups with 50 subjects in each group: 1 = AEx, 2 = LCh, 3 = AEx + LCh, and 4 = control. In addition, two age-matched reference groups (5 = pre-diabetes without NAFLD (n = 50) and 6 = Healthy without pre-diabetes or NAFLD (n = 50)) are included. The exercise program consists of progressive and variable aerobic exercise (intensity of 60 to 75% of initial fitness level, 3–5 times/week and 30–60 min/time). The diet program includes dietary consultation plus supplementation with a special lunch meal (40% of total energy intake/day) which aims to reduce the amount of carbohydrate consumption (30%). The control and reference groups are advised to maintain their habitual habits during the intervention. The primary outcome measures are HFC, serum metabolomics and gut microbiota composition. The secondary outcome measures include body composition and cytokines. In addition, socio-psychological aspects, social support, physical activity and diet will be performed by means of questionnaire and interview.

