### Primary and secondary outcomes

#### Primary outcomes

1. Liver fat content

2. Serum metabolomics, level of glucose, insulin, triglycerides and free fatty acids

3. Gut microbiota composition

The measurements of liver fat content, variables related to glucose metabolism, triglycerides and free fatty acids will be assessed at baseline and 6-month follow-up; gut microbiota composition will be measured at baseline, 3-month and 6-month time points.

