#### Fecal samples collection

The fecal samples (two samples per each time) will be collected during the second day of the 3-day dietary records collection. Detailed sample collection and transportation instructions are given by a study nurse. The study will provide to subjects the materials for sample collection and transportation from home to health care centre which including: 1 cool box, 2 plastic specimen jars (the cover of the jar contains the spatula), plastic bag, 4 cold chargers and plastic gloves. The subjects are advised to sample approximately 2–3 grams of feces by spatula attached to the cover of the plastic specimen jar. Then put fecal samples into the specimen jar and close it. The jars are stored in a plastic bag with the cool box. After samples are collected, the subjects will immediately deliver the samples to the health care centre (mostly about 5–10 min walking distance). If the subjects are not able to deliver the sample by themselves, the will call our research line and a personal from research group will pick up the samples from subjects home within 30 min to 1 hour.

Fecal samples are frozen after collection, stored at −80°C, and the DNA will be extracted with a fully automated instrument using magnetic beads-based technology (Genoextract, Hain Lifescience GmbH, Germany). Whole-genome sequencing will be performed using Illumina Hiseq 2000 system. In addition, fecal bacteria composition will be analyzed with a method based on flow cytometry, 16S rRNA hybridization, and DNA-staining. Different bacterial indices will be calculated to evaluate the inter-relationship of different bacterial species and how they are associated with liver fat content [8]. Concentrations of short chain fatty acids (SCFAs) will be determined in the supernatant using an Agilent 6890 N gas chromatograph with flame ionization detection and using ChemStation software for data processing.

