### Statistical methods

All data collected by questionnaires will be entered into database management software (Filemaker Pro version 10, FileMaker Inc. Santa Clara, CA, USA), double checked by independent researchers, and exported to PASW statistics version 20 (IBM Corporation, USA). If data is not normally distributed, their natural logarithms will be used for further analysis. Descriptive statistics will be used to present the background and anthropometric data at the baseline and follow-up assessments as mean and 95% confidence interval (CI) unless otherwise stated.

An intention-to-treat (ITT) analysis will be performed to compare the AEx, LCh and AEx + LCh groups to Con group. The effects of the interventions will be assessed using analysis of variance (ANCOVA) for repeated measures (treatment group × time) and baseline difference as a covariate. If the significance of the group by time interaction is p < 0.05, the effect will be localized utilizing Bonferroni for multiple comparisons. The level of statistical significance chosen for the contrasts will be p < 0.05. In addition to the ITT analysis, efficacy or active treatment analysis will be done when the compliance of the participation of the intervention is ≥60% of the whole trial and for <60% not more than 3 months continuously [ANCOVA for repeated measures (treatment group × time) and baseline difference as a covariate.] The percentage differences (0–6month) will be calculated from duration between baseline and end point measurements for each individual. The comparison of percentage changes in different groups will be performed using ANCOVA (two factor interactions: compliance/noncompliance × treatment group) controlled for the baseline value using Bonferroni for multiple comparisons. If the significance of the overall group difference is p < 0.05, then the effect will be localized by contrast to the Con group. When the 95% CI does not include zero, the difference is regarded as statistically significant at α = 0.05.

Linear Pearson’s correlation, partial correlation, Kendall Tau’s, and bivariate, logistic, and multivariate regression analysis will be used for analysing relationships. In addition, systems biology approaches will be used to develop models which integrate the different types of data and the high-throughput data measured in terms of gut microbiota composition and fecal SCFAs content, as well as LPSs and inflammation.

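### One general log/ANCOVA/correlation plan also covers gut microbiota, a primary outcome partly measured as shares, so one dominant taxon's response can be credited to taxa that did not change

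*Protocol article*

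**What the plan says.** The abstract states: "The primary outcome measures are HFC, serum metabolomics and gut microbiota composition". Under Primary outcomes, "gut microbiota composition will be measured at baseline, 3-month and 6-month time points".

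Fecal samples collection describes two assays. For the first, "Whole-genome sequencing will be performed using Illumina Hiseq 2000 system"; no spike-in or scaling to total load is described. For the second, "fecal bacteria composition will be analyzed with a method based on flow cytometry, 16S rRNA hybridization, and DNA-staining"; the units of its output are not given. The section continues: "Different bacterial indices will be calculated to evaluate the inter-relationship of different bacterial species and how they are associated with liver fat content". The indices are not defined.

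Statistical methods gives one transformation: "If data is not normally distributed, their natural logarithms will be used for further analysis". It gives one main model for arm effects: "The effects of the interventions will be assessed using analysis of variance (ANCOVA) for repeated measures (treatment group × time) and baseline difference as a covariate". Percentage changes from 0 to 6 months are also compared by ANCOVA. For associations it says: "Linear Pearson’s correlation, partial correlation, Kendall Tau’s, and bivariate, logistic, and multivariate regression analysis will be used for analysing relationships". The next sentence adds systems-biology models for the high-throughput microbiota data, as a supplement to these methods. Sample size estimation mentions projection methods for whole-genome data, says that they lack inference methods, and proposes path analysis.

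**The concern.** The number of reads per sample reflects the sequencing run, not how many bacteria the person carries. Without a load measurement, each taxon is known only as a share, and shares sum to one. If one taxon grows, the shares of all the others must fall even though their numbers are unchanged. Taking the natural log of each share rescales the values but leaves that dependence in place. The log is also undefined for a zero count, as is a percentage change from a zero baseline.

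Two things are at stake. Correlations between taxa can arise from the arithmetic of shares alone. In arm comparisons, a true response in one abundant taxon can be read as changes in several others. The trial wants to explain liver-fat change through specific changes in microbiota, so naming the wrong taxa would weaken the primary microbiota result and the path models built on it.

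**Working it through.** **The plan's own figure.** The only numerical design figure is 34 per group for 85% power on liver fat, at 0.05 with Bonferroni for 10 comparisons. No difference or SD is given, so it can only be inverted (two-sided alpha assumed): d = √(2/34) × (2.807 + 1.036) = 0.93. It does not bear on this point, and there is no microbiota figure to reproduce.

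**Closure by formula.** If a taxon with share s is multiplied by k and nothing else changes, every other share is multiplied by 1/(1 + s(k − 1)). For a doubling:
- s = 0.05: 1/1.05 = 0.95
- s = 0.10: 1/1.10 = 0.91
- s = 0.30: 1/1.30 = 0.77
- s = 0.50: 1/1.50 = 0.67

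The centred log-ratio (CLR) is ln x_j minus the mean of ln x over the D taxa. An unaffected taxon's CLR moves by −ln(k)/D. With D = 50 and k = 2 this is −0.693/50 = −0.014, about a 1.4% fall.

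**Arm contrast by simulation.** From the documents: 50 per group and 15% drop-out, so 50 × 0.85 = 42.5, taken as 42. Assumed: 50 taxa, log-SD 0.8, baseline/follow-up correlation 0.5, one active arm against control, one follow-up, baseline-adjusted ANCOVA, two-sided 0.05, 1,000 runs (Monte Carlo SE at 5%: √(0.05 × 0.95/1000) = 0.7 points). Rate at which one unaffected taxon is called significant:

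| Responder's share | Fold change | Log absolute | Log share | CLR |
|---|---|---|---|---|
| any | none | 5-6% | 5-6% | 5-6% |
| 5% | 2 | 7% | 8% | 6% |
| 5% | 4 | 4% | 14% | 5% |
| 10% | 2 | 5% | 9% | 5% |
| 10% | 4 | 5% | 33% | 6% |
| 30% | 2 | 5% | 28% | 5% |
| 30% | 4 | 4% | 92% | 5% |
| 50% | 2 | 4% | 50% | 4% |
| 50% | 4 | 5% | 99.8% | 6% |

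The average apparent change in the unaffected taxon after a doubling was a factor of 0.95, 0.91, 0.80 and 0.71 for the four shares. This is close to the formula; the gap at high shares comes from variation between people in the responder's share.

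A separate two-arm run under assumed settings (42 per arm) gave 33-48% when a taxon holding 30-40% doubled, and 6-7% when one holding 5% doubled. With log-SD 2 and sparse counts it gave only 5-7%.

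**With an overall test and Bonferroni step.** Assumed: four arms of 42, 30 taxa, log-SD 0.8, baseline correlation 0.6, one follow-up, overall test at 0.05, then Bonferroni over 6 pairs, with the responder doubling in all three active arms. Log-share results for an unaffected taxon:

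| Responder's share | Per contrast with control | Any of the three contrasts |
|---|---|---|
| 5% | 1.5% | 3% |
| 10% | 2% | 5% |
| 20% | 6% | 14% |
| 30% | 12% | 27% |
| 40% | 21% | 41% |

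The nominal level per contrast here is 0.05/6 = 0.8%.

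**Correlation of truly independent taxa.** n = 200 (4 × 50), log-SD 0.8 assumed:

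| Community | r, shares | r, log shares | Log-share tests with p < 0.05 |
|---|---|---|---|
| 5 equal taxa | −0.25 | −0.18 | 76% |
| 10 equal taxa | −0.11 | −0.08 | 19% |
| 50 equal taxa | −0.01 | −0.01 | 4% |
| 50 taxa, one at 50% (two minor taxa) | +0.08 | +0.16 | 62% |

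In a further simulation of 30 species, correlating CLR values of two abundant independent species gave about 8% significant, against about 5% on absolute counts. CLR thus removes most of the correlation problem but not all of it.

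**The case against.** A reader might infer that the plan commits the microbiota data to Pearson and Kendall correlation, and that unaffected species will come out significant with no biological change. The documents do not support either reading.

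- The correlation sentence names no variable. The sentence after it names microbiota and assigns it to systems-biology models. The log rule follows a sentence about questionnaire data.
- The bacterial indices are undefined and are introduced directly after the flow-cytometry assay. They could be ratios, which closure does not affect, or cell counts. The microbiota outcome may therefore not exist only as shares.
- With no responder, randomization holds the arm contrasts at about 5%. The inflated rates need a true response in an abundant taxon, which is a real change in composition. The error lies in which taxon is credited.
- With many even taxa, a small responder or high variability, the error is near nominal, and the overall test with Bonferroni lowers it further.
- Normalisation and zero handling are often left to an analysis plan or full protocol, neither of which is shown.

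The first four limit the point to what can happen, and they are accepted. The last stands for pipeline detail: the mere absence of a log-ratio step is no error. It does not dispose of the point, because the article states a transformation and models in general terms and exempts no outcome. The systems-biology models are additional to these, and the article itself says that projection methods lack inference. ANCOVA is therefore the only stated test of an arm effect on microbiota.

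**Conclusion.** The point holds in limited form. Followed as written, the plan allows sequencing shares of a primary outcome into raw or log ANCOVA and ordinary correlation, and a plain log does not correct for the fixed sum. Independent taxa can look correlated, and a dominant taxon's true response can be attributed to others.

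For one unaffected taxon, the error per unadjusted two-arm contrast runs from about 5% to roughly 30-50% when a taxon holding 30-50% of the community doubles. With the overall test and Bonferroni step it was 12-21% per contrast for a taxon holding 30-40%. CLR kept the two-arm rate at about 4-6%. Number of taxa, their evenness, variability and size of response are all assumptions and drive the result. The conclusion also depends on the data being analysed as shares, which the article neither states nor excludes.

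**What to change.** Add to Statistical methods that sequencing-derived taxon data enter the ANCOVA, correlation/regression and path models in one of two forms:

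- log-ratios, for example CLR with a zero-replacement rule fixed in advance; or
- absolute abundances (share × total bacterial count per gram), if the planned flow-cytometry/DNA-staining assay yields total counts.

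State there that taxon-taxon relationships use a composition-aware measure such as proportionality. In Fecal samples collection, say what the second assay reports and how the indices are defined.

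The cost is some wording and a little programming, with no new samples or assays. Log-ratio effects are harder to explain and depend somewhat on the zero rule, so an analysis on log shares can be kept as a sensitivity analysis.

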### Ethical issues, research permits or information permit applications

The current study will continue to adhere to all relevant guidelines for good scientific and clinical practice. All subjects in this study are volunteers. None of the measurements are known to have any significant health risk. The benefits and associated risks of the study will be carefully explained to the subjects and voluntary participation will be stressed. Informed consent will be obtained from all subjects. The study physician will be available during the laboratory tests. The study has been approved by Ethics Committee of Shanghai Institute of Nutrition, 06.01.2013, ref: 2013–003 and has registered in International Standard Randomized Controlled Trial Number Register (ISRCTN 42622771).

All data will be handled and archived confidentially. All the samples will be coded by ID number without personal information. All image scans and background information will be electronically transferred and stored in the specific database. The blood samples and fecal samples will be stored at -80°C. If the analyses will be performed outside the data collection site, the sample transportation will be handled according to the relevant safety standards. The duration of the sample storage is generally 10 years. If the samples storage time are exceeds the permitted time, a new permit will be obtained from both the subjects and the Ethical committee. If the subjects are deceased, permission will be sought from the relatives.

## Discussion

NAFLD is a very prevalent and severe disease which can lead to cirrhosis, liver carcinoma and death related to liver morbidity [29]. Meanwhile, epidemiological studies showed that 25% of patients with pre-diabetes progress to type 2 diabetes in 5 years [30] and several prospective studies even suggested that the rate may be even higher, averaging 10-12% annually [31-33]. Recent studies have reported novel mechanisms for the pathogenesis of NAFLD and diabetes, especially involving the gut microbiota [34,35]. However, the studies that have suggested a role of the gut microbiota in NAFLD and diabetes have been mainly conducted in animal models [35,36]. In addition, it is not clear whether NAFLD is due to impaired glucose metabolism or vice versa. There are very few studies examining the link between gut microbiota and the development of NAFLD in humans. Moreover, the relationship between gut microbiota composition and different nutritional status and physical activity has been explored mainly in animal models, but not in humans [36]. To the best of our knowledge, the AELC-study is the first study that includes specific lifestyle intervention attempting to modify patients’ diet and physical activity, which are expected to change the gut microbiota composition and therefore reduce the severity of NAFLD and prevent diabetes.

We expect that both exercise and diet intervention will induce favourable changes in gut microbiota composition thus improving metabolic state, and further reducing liver fat content and prevent development of diabetes. We also anticipate that the combined exercise and diet intervention will be more effective intervention than exercise or diet alone. The further follow-up after intervention of the study will serve as a pilot for future large scale studies to evaluate how, in practice, exercise and diet programmes can sustain their positive impacts on health in these high risk populations.

From a clinical point of view, using lifestyle intervention offers a novel approach for liver fat reduction and diabetes prevention through modification of gut microbiota composition, and highlights the importance of incorporating fitness assessment and prescription in the management of patients with fatty liver disorders [21,22,37] and high risk of diabetes [9]. However, the challenge is how to motivate the inactive people who are at high risk for metabolic disorders and who really need to escape from unhealthy lifestyles, to start and, more importantly, to maintain regular exercise. Therefore, this study will focus also on implementing strategies to promote behaviour change including regular contact and assessment with a health care professional, self-monitoring, and personalization of goals to change physical activity and unhealthy diet behaviour.

This research using specific lifestyle interventions offers a novel approach for liver fat reduction and diabetes intervention via modification of the gut microbiota composition, and explores the importance of incorporating fitness assessment and exercise in the management of patients with pre-diabetes and fatty liver disorders. If our program is shown to be effective, it will open new strategies to combat these chronic diseases.

## Trial status

Participant recruitment started in January 2013. Baseline measurement started in March 2013 for the first enrolled group. Exercise, Diet, and Exercise plus diet interventions started in March 2013. The recruitment of subjects is continuing until June 2014.

## Abbreviations

1H MRS: Proton magnetic resonance spectroscopy; AEx: Aerobic exercise; BM: Bone mass; BMI: Body mass index; COMP: Cartilage oligomeric matrix protein; Con: Control group; CRP: C-reactive protein; CVDs: Cardiovascular diseases; DXA: Dual-energy X-ray absorptiometry; FM: Fat mass; FGF23: Fibroblast growth factor 23; HDL: High-density lipoprotein; HFA: Hepatic fat accumulation; IL-1Ra: Interleukin-1 receptor antagonist; IL-1β: Interleukin 1β; IL-6: Interleukin; IR: Insulin resistance; LCh: Low carbohydrate diet; LDL: Low-density lipoprotein; LM: Lean tissue mass; LPS: Lipopolysaccharides; MEPE: Matrix extracellular phosphoglycoprotein; MRI: Magnetic resonance image; MVC: Maximal isometric voluntary contraction; MUFA: Monounsaturated fattyacids; NAFLD: Non-alcoholic fatty liver disease; PHEX: Zn-metalloendopeptidase; PUFA: Polyunsaturated fatty acids; Ref1: Pre-diabetes without NAFLD group; Ref2: Healthy reference group; SAFA: Saturated fatty acids; SCFAs: Short chain fatty acids; SLGI: Systemic low-grade inflammation; T2D: Type 2 diabetes; TNFα: Tumor necrosis factor alpha.
